## Abstract

**Introduction:**

Pharmaceutical drugs are beneficial to inflammatory conditions but with side effects, which led to the search for alternative therapies. *Perna canaliculus*, the New Zealand green-lipped mussel, have shown promise in placebo-controlled trials for inflammatory conditions. Fucoidan, an extract from seaweed *Undaria pinnatifida*, has been found to have beneficial effects on joint pain and insulin resistance. However, green-lipped mussel and fucoidan have never been combined.

**Methods and analysis:**

A parallel, two-arm, double-blind, randomized, placebo-controlled trial will be conducted in New Zealand to determine whether a food product supplemented with green-lipped mussel and fucoidan improves joint pain and/or insulin resistance. Those who are ethnically Chinese, are aged over 30 years, have prediabetes and hip or knee joint pain will be eligible to participate. They will be randomized at 1:1 ratio to consume either dark chocolate supplemented with 1000 mg mussel powder and 1000 mg fucoidan or dark chocolate with no active substances daily for 100 days. The primary endpoints are change in insulin resistance and patient-reported joint pain. Secondary endpoints include anthropometry, fasting glucose and insulin, HbA1c, inflammatory markers, satiety, quality of life, physical function, pain intensity, and analgesic medication use. A sample size of 150 (75 per arm) will provide 90% power at an overall significance level of 5% (two-sided) to detect a standardized effect size of 0.625 on either of the two co-primary outcomes allowing for 10% loss.

**Ethics and dissemination:**

The study was approved by the Health and Disability Ethics Committee (number: 20/STH/153). Results will be made available to participants, funders, and other researchers.

**Discussion:**

This trial will provide data on the potential utility of a mussel-fucoidan supplement in reducing joint pain and/or insulin resistance, to inform the development of a supplemented food product suitable for the Chinese market.

**Clinical trial registration:**

https://trialsearch.who.int/Trial2.aspx?TrialID=ACTRN12621000413820, ANZCTR Registration: ACTRN12621000413820, on 15 April 2021.

## Introduction

Inflammatory conditions, such as chronic musculoskeletal joint pain and insulin resistance, strongly contribute to the global burden of disease. Osteoarthritis and other causes of chronic musculoskeletal joint pain combined leads to an estimated 21.3% of the total years lived with disability globally (1). Chronic joint pain also impacts an individual's quality of life, participation in work and social activities, and economic independence (1). Type 2 diabetes, characterized by insulin resistance, is also a global health issue with prevalence rates rising (2). Diabetes is a major cause of blindness, kidney failure, cardiovascular disease, and lower-limb amputations (2). Therefore, preventative measures to avoid diabetes, joint pain, and their complications is a global challenge. Although pharmaceutical drugs for both chronic joint pain and diabetes are beneficial, they also have considerable costs and experienced side effects (3). Investigating potential alternatives to these pharmacological therapies is warranted.

One potential complementary therapy stems from *Perna canaliculus*, the New Zealand green-lipped mussel, which is native to the New Zealand coast. Nutritional supplements for inflammatory conditions, such as osteoarthritis, which contain *P. canaliculus* extracts, have shown promising results in placebo-controlled trials (4, 5). A six-month study evaluated the effect of Lyprinol^®^, a lipid extract of *P. canaliculus*, among 80 Chinese patients with knee osteoarthritis (6). There was a significantly greater reduction in perceived pain, and improvement in patients' global assessment of their arthritis, among those who took Lyprinol^®^ when compared with controls. Thus, the potential use of *P. canaliculus* for joint pain should be explored further.

A waste product of the mussel harvest process is *Undaria pinnatifida*, a species of New Zealand seaweed that infests the lines of mussel farms and interferes with the mussel harvest machinery (7). However, this seaweed species may also provide another potential complementary therapy. Polysaccharides called fucoidans can be extracted from *U. pinnatifida* and have been found to have various bioactive properties in *in vitro* models (8–11). Fucoidan extracts from other algal species have been shown to have anti-inflammatory effects and decrease the symptoms of osteoarthritis among a small sample of adults with knee osteoarthritis (12). In an animal study, it has been shown to inhibit carrageenan-induced oedema and ameliorated mechanical allodynia (13). *In vitro* studies also suggest that fucoidan may have preferential inhibition effect on cyclooxygenase-2, hence exhibit anti-inflammatory property (14). Therefore, it has the potential to be used for joint pain.

Fucoidan extract from *U. pinnatifida* has also been found to inhibit starch hydrolysing enzymes, such as α-amylase and α-glucosidase (8), which can slow down the digestion of carbohydrates. It may also improve insulin-stimulated glucose uptake and inhibit basal lipolysis in adipocytes without inducing adipogenesis, as previously shown using an *in vitro* model (15). Fucoidan mixed with traditional Chinese medicine has also demonstrated protective effects in diabetic rats, suggesting possible use for the treatment of diabetes mellitus (16). A recent clinical trial conducted in Australia (*n* = 72) investigated whether fucoidan extract reduced insulin resistance in an obese, non-diabetic population (17). Participants took capsules of either fucoidan/polyphenol extract (500 mg from *Fucous vesiculosus*) or a placebo. After 90-days of twice-daily supplementation, insulin resistance remained unchanged, as calculated using the homeostasis model of assessment (HOMA) score. However, participants had normal glucose tolerance (18). Recruiting individuals with established insulin resistance, such as prediabetes, may have illustrated more clinically meaningful effects.

Products containing fucoidan extracts have attained regulatory approvals in certain countries for use in foods and dietary supplements (19). The Food and Drug Administration in the United States of America (USA) permits consumption of fucoidan extracts from *U. pinnatifida* and *F. vesiculosus* at levels of up to 250 mg per day. Although, recent studies have used larger doses and reported no signs of clinical toxicity (12, 20, 21). Fucoidan extracts have particularly gained interest in China, such as the Haikun Shenxi Capsule of which the main active component is fucoidan, which has been approved for treating renal diseases (22).

Combining green-lipped mussel and fucoidan extracts is a novel innovation and may produce additive benefits. To our knowledge, this is the first study to test the anti-diabetic and joint pain effects of this combination. Therefore, this trial aims to gain new knowledge into the bioactivity of a mussel-fucoidan combination, particularly focusing on its potential effects on inflammation and glycaemic control. The results of this trial will help us to better understand the use and effectiveness of mussel-fucoidan health products among the Chinese population and will help inform product development for the Chinese market.

## Methods/design

### Trial aim and hypothesis

The primary objective of this trial is to determine whether a food product supplemented with green-lipped mussel and fucoidan powder improves joint pain and/or insulin resistance. We hypothesize that the mussel-fucoidan combination will be superior to placebo in reducing patient-reported joint pain and/or improving insulin resistance.

### Trial design

A parallel, two-arm, double-blind, randomized, placebo-controlled trial will be conducted in Auckland, New Zealand. The trial steering committee is located at the Auckland University of Technology (AUT) North Shore campus. Ethical approval was granted by the Health and Disability Ethics Committee (HDEC; reference number: 20/STH/153). The protocol was prepared following Standard Protocol Items: Recommendations for Interventional Trials (SPIRIT) statement (**Additional File 1**). The CONSORT flow diagram is present in Figure 1. The funding application including the trial design has been reviewed by the funding agency the New Zealand National Science Challenge – High Value Nutrition.

**Figure 1 F1:**
[figure not shown]
CONSORT diagram.

### Patient and public involvement

We invited eight people who met the proposed eligibility criteria to participate and provide feedback on the trial design *via* telephone interviews. They were generally supportive of the trial; feedback centered on the proposed recruitment methods, the trial schedule of assessments and data collection, and methods for disseminating results. Engaging with this group supported the refinement of the trial design to ensure that the study protocol is feasible and that the outcomes are valuable to key stakeholders.

### Participant characteristics

Participants will be recruited through primary healthcare organizations, general practices, Asian health organizations, and advertising in Chinese media. Adults who are ethnically Chinese and live in Auckland, New Zealand, will be invited to participate in this trial. The eligibility criteria are presented in Table 1.

**Table 1 T1:** Trial eligibility criteria.

**Inclusion criteria (all)**	**Exclusion criteria (any of the below)**
• Of Chinese ethnicity (both parents are ethnically Chinese) • Lives in Auckland • Aged over 30 years • Able to speak and understand English and/or Mandarin • HbA1c between 41 and 49 mmol/mol at screening • Ongoing knee or hip joint pain for the last 3 months or longer (i.e. diagnosed with osteoarthritis) • Owns a smartphone or tablet, has access to an Internet connection, and is willing to use the WeChat app	• Diabetes (type 1 or 2) • Known or suspected seafood (fish and shellfish) allergy • Currently taking a green-lipped mussel supplement • Previous joint replacement surgery, or planning this within the next six months • Pregnant or breastfeeding, or intending to become pregnant within the next 6 months • Previous bariatric surgery • Conditions that may influence body weight regulation (e.g. malabsorption, thyroid disorders) • Taking any glucose-lowering medications, systemic steroids, or blood thinners • History of thalassemia, asthma, gout, liver disease, kidney disease • Planning major changes to physical activity within the next 6 months • Significant weight loss or weight gain within the last 6 months • Fear of needles or giving blood • No access to a smartphone, tablet, or Internet

### Informed consent

All participants will be screened for eligibility based on the outlined criteria. Participants will be encouraged to discuss their involvement in this trial with others and ask the research team any questions before agreeing to participate. The principal investigator (PI) will ensure all participants provide written informed consent before data collection. All participant-facing documents will be available in both English and Mandarin. During data collection, research assistants fluent in both English and Mandarin will be present to support the participants' engagement in the research process. Participants can withdraw at any time.

### Preparation of the mussel-fucoidan test food and placebo

Mussel powder was supplied by Cfarmx New Zealand Limited (Auckland, New Zealand). The powder contains around 5% moisture, 12% lipid, 55% crude protein, 22% ions (ash) and 5% carbohydrate. The omega-3 lipid content is more than 2%. New Zealand green shell mussels are sustainably farmed with little environmental impact and are rated by the Monterey Bay Seafood Watch Programme as one of the most sustainable seafood products in the world. Seaweed sporophylls have been purchased from a New Zealand supplier and processed by NZ Extract Limited (New Zealand), Callaghan Innovation (New Zealand), and Alaron Products Limited (New Zealand) to produce 25 kg of fucoidan. The fucoidan product contains around 70% carbohydrate, 28% ions (ash) and 1% protein. The fucose and xylose content is more than 20% each, the sulphation level is around 25%, and the average molecular weight is around 330 kDa. The fucoidan produced was used to formulate a mussel-fucoidan food product in the food laboratory of AUT in Auckland, New Zealand. The food product has been tested for flavor and consumer acceptability. Alaron Products Limited manufactured the mussel-fucoidan prototype food product according to our formulation. Beyond Capital MedTech Management Limited has acquired the necessary food product certifications for the batch of fucoidan used, as well as the prototype food product.

### Randomization and concealment

Eligible participants will be randomly assigned to receive either the mussel-fucoidan prototype product or the placebo in a 1:1 ratio. The trial biostatistician will prepare the blinded randomization lists using permutated block randomization with variable block sizes. Random pack numbers will be generated in the drug labeling list and pre-packed in identical boxes by Alaron Products Limited. Once a participant has provided informed consent and has been confirmed eligible to be randomized, the database will show the pack number linked to the participant in the allocated group. A research assistant will provide participants with their correct treatment packs, with no information on actual group allocation. Neither the participant nor any research team member will know the treatment product indicated by the randomization. During the trial, the blind may be broken in emergencies, such as when knowledge of the participant's treatment group is necessary for further participant management.

### Interventions

All participants will receive either the treatment intervention or a placebo for 100 days. The mussel-fucoidan prototype product will be 20 g of dark chocolate containing 1000 mg of mussel powder and 1000 mg of fucoidan extract. The placebo will be 20 g of dark chocolate, without any active substances. Each dose will be individually and identically packaged. The prototype product and placebo have been determined as indistinguishable by sensory panelists. Participants will be encouraged to eat *ad libitum* over the 100-day period but will be advised of the caloric value of the dark chocolate should they wish to substitute foods with an equivalent caloric value. Participants who miss one dose will be encouraged to take two doses the following day to a maximum of two doses per day. The risk of overdosing is minimal as both fucoidan and mussel are food product with a GRAS (generally regarded as safe) status in FDA category.

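### The overdose statement rests on FDA status alone, but the FDA level the article quotes for fucoidan is a quarter of the daily portion and an eighth of a catch-up day's intake

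*Protocol article*

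**What the plan says.** Three statements in the protocol article bear on this point.

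- **Exposure (Interventions; Abstract, Methods and analysis).** Each 20 g portion in the active arm is "dark chocolate containing 1000 mg of mussel powder and 1000 mg of fucoidan extract". The Abstract makes this a daily portion for 100 days.
- **Missed portions (Interventions).** "Participants who miss one dose will be encouraged to take two doses the following day to a maximum of two doses per day". The reason follows directly: "The risk of overdosing is minimal as both fucoidan and mussel are food product with a GRAS (generally regarded as safe) status". The sentence ends by placing that status with the FDA. It gives no amount and refers to no study.
- **Regulatory background (Introduction).** The FDA is said to permit fucoidan extracts from *U. pinnatifida* and *F. vesiculosus* "at levels of up to 250 mg per day". The next sentence qualifies this: "Although, recent studies have used larger doses and reported no signs of clinical toxicity (12, 20, 21". The doses in those studies are not given.

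**The concern.** The Interventions section uses FDA status as the whole argument for minimal overdose risk, without a quantity. The Introduction attaches a quantity to FDA permission for the same kind of extract, and both planned exposures exceed it. A reader who puts the two sections together finds that the reason given does not reach the amounts it is meant to cover.

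What is at stake is the soundness of a stated safety basis. The protocol does not merely tolerate a double portion; it encourages one. Whoever judges that instruction should be able to see which evidence supports the regular daily amount and which supports twice that amount. At present the sentence offers one reason for both. No endpoint, estimate, sample size or analysis depends on this.

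**Working it through.** There is no statistical figure to reproduce. The check is a ratio of the article's own amounts.

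**Inputs**

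- Permitted level, fucoidan extract: up to 250 mg per day (Introduction).
- Fucoidan extract per portion: 1000 mg (Interventions).
- Portions per regular day: 1 (Abstract). Portions per catch-up day: at most 2 (Interventions).
- Source species: *U. pinnatifida* (Abstract: "Fucoidan, an extract from seaweed *Undaria pinnatifida*, has been found" to have the effects under study). This is one of the two species named with the 250 mg level. Both sections speak of an extract, so the comparison is like for like.

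**Formula:** ratio = (portions × mg per portion) ÷ permitted level

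- Regular day: 1 × 1000 = 1000 mg; 1000 ÷ 250 = **4.0**
- Catch-up day: 2 × 1000 = 2000 mg; 2000 ÷ 250 = **8.0**
- Missed day and catch-up day averaged: (0 + 2000) ÷ 2 = 1000 mg per day; 1000 ÷ 250 = 4.0

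**Sensitivity to composition.** The section on preparing the test food says: "The fucoidan product contains around 70% carbohydrate, 28% ions (ash) and 1% protein". Suppose, as an assumption, that only the 70% carbohydrate fraction counted against the permitted level:

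- Regular day: 0.70 × 1000 = 700 mg; 700 ÷ 250 = 2.8
- Catch-up day: 0.70 × 2000 = 1400 mg; 1400 ÷ 250 = 5.6

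Both exposures stay above the quoted level.

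**Other dose information in the article.** The Introduction describes a 90-day trial (n = 72) of 500 mg of a fucoidan/polyphenol extract taken twice daily. Read as 2 × 500 = 1000 mg per day, this equals the regular portion and is half the catch-up amount. The extract came from *F. vesiculosus*, and the article reports the trial's insulin-resistance result but no safety result.

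**The case against.** The best defence has four parts.

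1. **The two statements can both be true.** The 250 mg figure is something the FDA permits, not a level above which harm is expected, and the Interventions sentence does not say in terms that the status extends to 1000 or 2000 mg. This stands as far as it goes: a reader might infer that participants are being given an unsafe amount, and the article does not support that. But the sentence offers the status as the reason why overdosing is unlikely to matter, and a reason has to reach the amounts it is given for.

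2. **The Introduction discloses the excess and answers it.** It cites studies at larger doses without clinical toxicity, and it describes a trial at about 1000 mg per day. This softens the point, most of all for the regular day. It does not settle it. The overdose statement does not draw on those studies, and the article does not say whether any reached 2000 mg per day. Equally, it cannot be asserted that they did not.

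3. **Catch-up does not raise the total.** A double portion follows a missed one and is capped at two per day, so the two-day total stays at the planned 2000 mg. That is correct. The factor of 8 describes the single day's intake only, and the two-day average remains at the factor of 4.

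4. **Safety monitoring is broader than the scheduled questions.** A reader might infer from the Day 30, 50 and 100 collection that events on double-portion days would go unseen. The Adverse events section does not support that: participants are encouraged to raise side effects with the principal investigator and their general practitioner, serious events go to the ethics committee, duration is recorded, and an independent committee reviews all events.

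A reader might also infer that the ethics committee or the participants were misinformed. The full protocol and the information sheet are not shown, so nothing can be said about what they were told.

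**Conclusion.** The safety rationale is internally inconsistent. FDA status is the sole stated ground for minimal overdose risk, while the article's own FDA figure for this extract is exceeded 4 times on a regular day and 8 times on a catch-up day (2.8 and 5.6 times if only the carbohydrate fraction is counted). On that figure the cited status supports neither exposure.

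The conclusion rests on one reading: that the status in the Interventions section and the permitted level in the Introduction describe the same FDA position. The article names no other. If they are different things, the text should say so and give the amount that the status covers.

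The point is limited to fucoidan, since no FDA level is given for mussel powder. It shows a stated reason that does not carry its conclusion. It does not show harm, and it does not show that the trial's exposure is wrong. It deserves correction because it concerns an instruction that participants are encouraged to follow, but it leaves the trial's statistical design untouched.

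**What to change.** - **Reconcile the Introduction and the Interventions section.** The overdose statement should name the evidence it relies on separately for the regular day and for the catch-up day, with the doses in the studies cited, and should state how the FDA status relates to the 250 mg per day level.
- **Ask the independent safety committee already provided for under Adverse events to review the catch-up instruction against that evidence.** The decision is the committee's and the investigators'; no dose or catch-up rule is proposed here.
- **Tabulate adverse events by double-portion days for that committee.** Participants already scan a code on each wrapper to log daily intake (Participant adherence). The table is possible if scan dates are stored, which the article does not say outright.

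Cost: a wording amendment with notification to the ethics committee, and one extra table from data already being collected.

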### Outcome measures

The primary endpoints are change in insulin resistance, defined by the HOMA values, and patient-reported pain measured by the Western Ontario and McMaster Universities Arthritis Index (WOMAC). Secondary endpoints include anthropometry, fasting glucose and insulin, glycated hemoglobin (HbA1c), inflammatory markers (C-reactive protein, tumor necrosis factor-alpha (TNF–α), interleukin (IL)-6, IL-2, IL-8, IL-1β, IL-10 and IL-4), physical function, quality of life, pain intensity, satiety on a VAS (0 = extremely hungry, 10 = extremely full), analgesic medication use, and parameters related to COX-2 inhibition. A 7-day food record and physical activity questionnaire will be collected pre- and post-intervention to determine any changes which may have influenced observed outcomes. The trial schedule of assessments and data collection is presented in Figure 2.

**Figure 2 F2:**
[figure not shown]
Trial schedule of assessments and data collection.

### Homeostasis model of assessment

The HOMA model is used to estimate insulin sensitivity using fasting plasma glucose and insulin concentrations (23). The liver and pancreatic β-cells function in a negative feedback loop, reflecting the balance between hepatic glucose output and insulin secretion. HOMA can be used to demonstrate the effects of an intervention on insulin resistance (24). The equation used to measure insulin resistance is (Fasting plasma insulin [mU/l) × Fasting plasma glucose (mmol/l)] ÷ 22.5.

